### Study arms

Forty-one schools were randomized to one of the three conditions; school-led FRIENDS, health-led FRIENDS or treatment as usual (control). One school in the control arm withdrew after randomization.

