### Economic evaluation

The analysis of the cost data, the CHU-9D data and cost-effectiveness analysis will be conducted according to current best practice methods for conducting economic evaluation alongside trials,
[37,38] and specifically alongside cluster-randomized controlled trials
[39]. Incremental costs, incremental effects, and where relevant incremental cost-effectiveness ratios (ICERs) will be estimated, comparing the three conditions. The incremental cost per unit quality-adjusted life year (QALY) increase will be estimated. Both unadjusted analyses and adjusted analyses will be carried out, adjusting for site, mode of delivery, number of students and number of classes.

Random effects bivariate linear regression models will be fitted to model cost and effectiveness (QALY) simultaneously, allowing for correlation within clusters and correlation between cost and effectiveness score within participants
[40]. From these models we will estimate: the mean difference in costs of the three conditions and corresponding standard error; the mean difference in effect and corresponding standard error; and, indirectly via the variance-covariance matrix of the regression coefficients, the correlation between the mean cost difference and the mean effect difference. Where the interventions are estimated to have both higher costs and greater effectiveness than control, we will use Fieller’s method to obtain a parametric estimate of the 95% confidence interval for the ICER and to construct the cost-effectiveness acceptability curve (CEAC). Both parametric and non-parametric bootstrap estimates of the confidence interval for the ICERs will be estimated.

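### The acceptability curve and Fieller interval are tied to a comparison with control, although the economic evaluation covers three competing conditions

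*Protocol article*

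**What the plan says.** All of this is in the protocol article, Methods/Design, Economic evaluation.

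- The scope covers all arms: "Incremental costs, incremental effects, and where relevant incremental cost-effectiveness ratios (ICERs) will be estimated, comparing the three conditions".
- A bivariate random-effects model of cost and QALY is to supply "the mean difference in costs of the three conditions and corresponding standard error", the corresponding effect difference, and "the correlation between the mean cost difference and the mean effect difference".
- Fieller's method is then to be used "to obtain a parametric estimate of the 95% confidence interval for the ICER and to construct the cost-effectiveness acceptability curve (CEAC"). This step is conditional: it applies "Where the interventions are estimated to have both higher costs and greater effectiveness than control".
- The section closes: "Both parametric and non-parametric bootstrap estimates of the confidence interval for the ICERs will be estimated". No comparator is named for these intervals.

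The section mentions no curve covering all three conditions and no Fieller interval between the two FRIENDS modes. Under Statistical analysis, the comparison of school-led with health-led delivery is called exploratory and underpowered. Costs and QALYs are not mentioned there.

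**The concern.** According to the Design section, the programme is delivered to whole classes within the curriculum. For a given class the three conditions are therefore alternatives, and the economic question is which one to choose.

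A CEAC exists to express uncertainty about that choice. The only concrete CEAC instruction uses control as its reference and lists one cost difference, one effect difference and one correlation as inputs. That describes a two-option curve. Two such curves, one per mode, would each answer whether the mode is worth having over usual curriculum. Neither would show how likely it is that the mode is the best of the three. A dearer mode could score well against control and still be poor value against the cheaper mode.

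The trigger raises a second difficulty. A condition on the quadrant of the point estimate is understandable for an interval on a ratio, which is hard to interpret elsewhere. It is not needed for a CEAC. If a mode's point estimate were cheaper than control, or less effective, the sentence would provide no curve for it, although sampling uncertainty could still span several quadrants.

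**Working it through.** **Plan's own figure.** The article states no threshold, cost difference, QALY difference or standard error for the economic evaluation, so there is nothing to reproduce. Every number below is assumed and shows the mechanism only.

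**Step 1: the general relation.** Net benefit is NB = λ × QALY − cost. The event that a mode has the highest NB of the three is contained in the event that its NB exceeds control's. Hence P(best of three) ≤ P(better than control) for any inputs. Only the size of the gap depends on assumptions.

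**Step 2: formula against control.** For a mode with cost difference ΔC and QALY difference ΔQ against control, and no cost–effect correlation:

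P(better than control) = Φ[(λΔQ − ΔC) / √(λ²·SE_Q² + SE_C²)]

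P(best of three) was obtained by simulating three independent arm means (400,000 draws), so that the two contrasts share the control arm.

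**Step 3: first assumed case.** λ = 20,000, SE_C = 25, SE_Q = 0.003. The cheaper mode is +30 and +0.003 QALY; the dearer mode is +60 and +0.004 QALY.
- SE of NB difference: √(60² + 25²) = 65.
- Cheaper mode: NB difference 60 − 30 = 30, z = 30/65, probability 0.68. ICER 30/0.003 = 10,000.
- Dearer mode: NB difference 80 − 60 = 20, z = 20/65, probability 0.62. ICER 60/0.004 = 15,000.
- Dearer against cheaper: ICER (60 − 30)/(0.004 − 0.003) = 30,000, above λ.
- P(best): control 0.20, cheaper mode 0.46, dearer mode 0.35 (rounded).

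**Step 4: second assumed case, over a range of precision.** λ = 20,000, SE_C = 10. Mode A is +40 and +0.008 QALY; mode B is +80 and +0.009 QALY. The NB differences from control are 160 − 40 = 120 and 180 − 80 = 100. B's ICER is 80/0.009 = 8,889 against control and 40/0.001 = 40,000 against A.

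| SE_Q | SE of NB difference | P(B better than control) | P(B better than A) | P(A best) | P(B best) |
|---|---|---|---|---|---|
| 0.002 | √(40² + 10²) = 41.2 | 0.99 | 0.31 | 0.69 | 0.31 |
| 0.004 | √(80² + 10²) = 80.6 | 0.89 | 0.40 | 0.58 | 0.39 |
| 0.008 | √(160² + 10²) = 160.3 | 0.73 | 0.45 | 0.49 | 0.40 |

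**Step 5: cost–effect correlation.** The plan models this correlation and Steps 3 and 4 set it to zero. In the first case, a correlation ρ changes the variance of the NB difference to 60² + 25² − 2ρ × 60 × 25. With ρ = 0.5 this is 2,725 (SE 52.2) and the dearer mode scores Φ(20/52.2) = 0.65 against control. With ρ = −0.5 it is 5,725 (SE 75.7) and Φ(20/75.7) = 0.60. Repeating the simulation of Step 2 with these standard errors leaves its probability of being best at 0.35 in both cases. The gap does not come from ignoring the correlation.

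**The case against.** The strongest reply is that the section never limits itself to control. It sets a three-condition scope for costs, effects and ICERs, takes cost differences across three conditions from the model, and plans bootstrap intervals for ICERs in the plural with no comparator named. Control appears once, in a clause saying when the Fieller interval and CEAC apply. This stands. A reader might infer that the plan compares each mode with control only, or would overlook that one mode is the better buy. The text does not support that: a school-led versus health-led ICER is within the plan, and it would reveal the 30,000 or 40,000 in the illustrations.

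A reader might also call it an error that the two curves in the first case read 0.68 and 0.62, a sum of 1.30. It is not. The two statements are not mutually exclusive, and each is correct for its own question. Uncertainty is understated only if a curve against control is read as a probability of being best, which the article does not say.

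Two further arguments stand in part. Control is a natural reference, since the trial was powered for FRIENDS against usual provision; that is a reason to keep those curves as a supplement. And a condensed article may leave dominance rules and the form of the curve to a fuller plan. But this article does not leave the CEAC open: it names its method, inputs and reference. Its general commitment to good current practice does not say how that instruction extends to three options.

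**Conclusion.** The point holds for the CEAC and the Fieller interval, not for the whole economic evaluation. The three-condition scope and the control-referenced sentence do not match, and the one curve described cannot show which of three options is likely to be best. That a mode's probability of being best cannot exceed its probability of beating control needs no assumption. The size does: in the assumed cases the dearer mode falls from 0.62 to 0.35, and from 0.73–0.99 to 0.31–0.40. These figures rest on an assumed threshold of 20,000, assumed differences and standard errors, independent arms of equal precision and, except in the correlation check, no cost–effect correlation. They are not forecasts for this trial. The missing curve outside the dearer-and-more-effective quadrant is a smaller gap in the same sentence. Severity is modest: the planned model is sound for the purpose, and between-mode ICERs are already within scope.

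**What to change.** Bring the Fieller/CEAC sentence into line with the three-condition scope.

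1. Build one CEAC that shows, over a range of thresholds, each condition's probability of having the highest net benefit. Use the joint covariance matrix of both cost contrasts and both effect contrasts, including the covariance from the shared control arm. Produce it whatever the quadrant of the point estimates.
2. Report ICERs and their intervals in a full incremental analysis: order the conditions by mean cost, remove dominated and extendedly dominated options, and compare each remaining option with the next best.
3. Label the school-led versus health-led economic comparison exploratory, as the Statistical analysis section does for outcomes.
4. Keep curves against control as a supplement if wanted, described as the probability of being cost-effective relative to usual curriculum.

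The cost is a change of wording and a little more analysis. The planned bivariate model already yields the matrix, and no new data are needed. The stated probabilities for each mode can only stay the same or fall relative to curves against control, and the text should say so.

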### Study status

The trial started in January 2011 and 41 schools were randomized although one subsequently withdrew. Baseline assessments and intervention delivery started in September 2011 and twelve-month assessments are scheduled to be completed by May 2013.

## Abbreviations

CEAC: Cost-effectiveness acceptability curve; CONSORT: Consolidated Standards of Reporting Trials; ICC: Intra-cluster correlation coefficient; ICERs: Incremental cost-effectiveness ratios; ITT: Intention-to-treat; PACES: Preventing Anxiety in Children through Education in Schools; QALY: Quality-adjusted life years; RCADS-30-P: Parent completed Revised Child Anxiety and Depression Scale; RCADS: Revised Child Anxiety and Depression Scale; RCT: Randomized controlled trial; SDQ: Strengths and Difficulties Questionnaire.
